**Figure 3 F3:**
[figure not shown]
**Flow diagram of clusters and participants in the trial**.

**Table 2 T2:** Research questions and associated trial outcome measures

Research question	Outcome measure	Data source
**LSSS Dataset**		

1. What is the rate at which the population of Pakistani and Bangladeshi male smokers will set a quit day with the stop smoking services in the intervention and control areas.	Recruitment rate is defined as the number of relevant population setting a quit day with the services as a fraction of all those estimated to have attempted to stop.	LSSS routine database

2. What proportions of those setting a quit day in the intervention and control areas achieve prolonged abstinence from smoking at a) 4 weeks, b) 3 months and c) 6 months after the agreed quit day?	a) Number of quits (measured by self assessment questionnaire & CO monitoring) Total number of smokers* accessing LSSS b) & c) number of quits (measured by self assessment questionnaire & CO monitoring)	a) LSSS routine database b) & c) LSSS data collected specifically for the trial

3. What is the likely degree of contamination of the intervention and control areas and the design effect that need to be considered when conducting sample size calculations for a definitive cluster randomised controlled trial?	The design effect from cluster randomisation will be calculated from the multilevel analysis. Contamination cannot be easily measured; however, we have external controls which will help indicate whether it is occurring.	

4. What are the key components of the intervention as it develops and how do these components relate to the outcome measured by the rates of setting quit dates and abstinence among those setting quit dates?	Qualitative data	Focus groups with outreach workers Observation of management meetings Shadowing Analysis of outreach worker diaries End of project interviews with outreach workers

5. What proportion of Pakistani and Bangladeshi male smokers that book an appointment with the stop smoking service attend the initial appointment and set a quit day in the intervention and control areas?	To be estimated from a sample of service providers records	SSA records LSSS Routine database

**Extended Dataset**		

6. What smoking cessation treatments do Pakistani and Bangladeshi men use in the intervention areas, facilitated by outreach workers, and in the control areas, without such workers?	Numbers of clients choosing each available treatment option (e.g. NRT, Zyban etc)	LSSS Routine database Patient satisfaction questionnaire administered by LSSS 'Call to Quit' team

7. What are the experiences of the services of the relevant groups in each of the trial arms and how satisfied are they?	Patient satisfaction	Patient satisfaction questionnaire administered by LSSS 'Call 2 Quit' team

8. What proportions of those enrolled adhere to the interventions chosen?	Numbers using oral tobacco during quit attempt (self report) Number of people adhering to each medication used in each arm of the trial (self report) Attendance at clinic in each arm of the trial	Adherence rating week by week then averaged, collected by SSA on extended data monitoring form

9. What impact, if any, are these interventions likely to have on smokeless (oral) tobacco use in these smokers?	Numbers using oral tobacco during quit attempt (self report)	Frequency rating week by week, collected by SSA on extended data monitoring form Frequency of use of oral tobacco during this quit attempt rating on Patient satisfaction questionnaire administered by LSSS 'Call to Quit' team

10. What are the costs, from a health service perspective, of delivering these interventions?	Estimated benefits of the intervention in terms of QALYs or LYGs.	Additional costs to NHS of (i) Employment, training, management of outreach workers- (ii) Extra resources used by LSSS – e.g. medication, behavioural support (Calculated from estimates of extra time used)

### Local Stop Smoking Service (LSSS) Dataset

#### Inclusion criteria

Any male (≥18 years) Pakistani or Bangladeshi using the NHS stop smoking services in the study areas will be eligible for inclusion in this study.

The LSSS routinely records abstinence rates at four weeks post quit date. Anyone from the target population who maintains abstinence at four weeks will be eligible for follow-up at three months. Service users will be contacted by the Birmingham 'Call 2 Quit' line – a special project to enhance the stop smoking services in Birmingham – and invited to attend a clinic appointment for verification of abstinence using expired carbon monoxide. Any service users who are still abstinent at three months will be followed up in the same way at six months.

#### Exclusion criteria

Any users of the NHS stop smoking services who are not from the relevant ethnic groups will be excluded. Anyone from the target population who does not maintain abstinence at four weeks will not be eligible for follow-up at three or six months.

#### Consent

Consent from patients will not be required as the data will be received from the Primary Care Trusts (PCTs) in an anonymised form.

#### Losses to follow-up

Loss to follow-up is not an issue in relation to the primary outcomes of use of services or abstinence. People who attend a stop smoking service set a quit date at one point in time or they do not, and only those who do are monitored by the LSSS. Furthermore, the other important outcomes (i.e. cessation at four weeks, and three and six months) are routinely monitored by the service too. As is standard protocol of smoking cessation research, people who are lost to follow-up are deemed to be smoking again[31,32].

### Extended Dataset

The aim of the Extended Dataset is to provide more detailed data on attendance and adherence than can be obtained from the NHS records and to provide information on service use satisfaction that cannot be obtained from NHS records. To accomplish this, Pakistani and Bangladeshi men using particular NHS services will be approached and asked for consent to provide this information to the research team.

#### Recruitment

A sub-sample of individuals who go through the NHS LSSS in these areas will be invited into a study of their perceptions of the service. We will recruit providers of NHS stop smoking services in both our study areas to collect this additional data. These will be drawn from those stop smoking advisors, nurses and pharmacists who provide smoking cessation services in or near the study areas that have, on past data, delivered stop smoking services for Pakistani and Bangladeshi men residing in the intervention or control areas. We will supply each SSA taking part in the extended data collection with a pack containing a brief procedure guide, information sheets, consent forms, data collection forms and a method to contact the study team. The baseline patient questionnaire incorporates items from a culturally valid tobacco use questionnaire[33]. Service users will be asked to participate by their service provider (outreach worker, nurse, specialist SSA or pharmacist) during routine consultation. These data will be supplied to the study team confidentially, but not anonymously.

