#### 'Clinic + outreach' (intervention)

In areas allocated to the 'clinic + outreach' arm, the NHS stop smoking services will attract clients with additional support from four community based stop smoking advisors, also known as 'outreach workers'. These outreach workers come from the ethnic groups of interest (i.e. two of Bangladeshi origin and two of Pakistani origin) and live in the communities that they serve. Between them, they speak several relevant languages (i.e. Sylheti, Bengali, Punjabi, Mirpuri, Urdu and English).

A specialised training programme for the outreach workers will be organised prior to the start of the intervention, to combine training in smoking cessation with a special understanding of the norms and beliefs about tobacco in the Pakistani and Bangladeshi communities. This will consist of:

◦ Standard two-day SSA training delivered by HoB tPCT

◦ Three-day health promotion training course delivered by HoB tPCT on exploring ways to promote well-being and health, and techniques involved in the planning, preparation and delivery of approaches.

◦ Sessions given by primary care staff at the University of Birmingham on research skills, communication skills, the function of the NHS, the cultural context of the work, and discussion of the outreach role.

We envisage that the outreach workers will take the following approaches to improve the reach of and access to the smoking cessation services:

◦ Undertake community engagement work to help increase awareness of smoking cessation services

◦ Assist existing service providers with the delivery of stop smoking support and promotions

◦ Provide stop smoking support and medication for people in non-clinic venues, e.g. workplaces, public buildings.

Additionally, we envisage that the outreach workers will draw on their in-depth understanding of beliefs about and attitudes towards smoking, in order to:

◦ Raise awareness of the dangers associated with smoking and counsel smokers wishing to quit

◦ Identify suitable quit dates (which may be based on key religious events such as a Friday congregational prayer, journey on Umrah or Hajj (pilgrimage to Mecca), or to coincide with the month of Ramadan, for example)

◦ Highlight religious objections to smoking, where appropriate

◦ Make available existing and custom-made literature, telephone (Asian QuitLine) and other support materials.

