The secondary questions will be addressed either through LSSS data on treatments used, or through an Extended Dataset collected from a self-selected sub-sample of participants in the trial (Extended Dataset). Data sources and outcome measures for each of these research questions are summarised in Table 2. The flow of participants through the trial is shown in Figure 3.

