#### Consent

Written consent will be obtained from all users prior to their inclusion in this extended data collection phase.

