#### Losses to follow-up

Those individuals recruited in the Extended Dataset will be asked about their satisfaction with the stop smoking service they received. It is the experience of LSSS that individuals who return to smoking do not return to clinic, while those who have succeeded do so and are typically very pleased with the care they received. Thus, loss to follow-up is a potentially major bias in assessing these outcomes. However, these individuals will have consented to follow up and thus we seek to minimise loss of information from those who do not stop smoking by telephone contact from the Birmingham Call 2 Quit line.

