#### Protocol amendments

From the time of writing this protocol, the following changes have been made.

We aimed to measure the rate at which Pakistani and Bangladeshi male smokers set a quit date with the stop smoking services in the intervention and control areas. We defined reach as the proportion of each relevant ethnic group setting a quit date using the stop smoking service, with the denominator for this being all those of relevant ethnic group attempting to quit during the same period. As this latter number could only be estimated, we investigated whether The Health Survey for England ethnic boosted sample data had the relevant information (i.e. the proportion that tried to stop in the previous year). These data did not, however, contain this information and we have therefore assumed that the proportion of Pakistani and Bangladeshi males that attempt to quit is the same as the proportion of all other ethnic groups. This assumes that what is true of the majority population is true of Pakistani and Bangladeshi populations.

Prior to the start of the study, the randomisation of the intervention and control areas were switched, as the initial allocation meant more Pakistani and Bangladeshi target populations resided in areas allocated to the control than intervention. The managers of HoB and BEN PCTs preferred that the outreach workers were given the opportunity to reach more people, thus, the randomisation was switched in consultation with the trial statistician and Independent Project Steering Committee.

Initially, we aimed to follow-up LSSS service users who achieved 4-weeks prolonged abstinence from smoking at three months from the agreed quit date. The Birmingham 'Call 2 Quit' line was unable to do this at three months. However six-month follow-up proceeded as planned.

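### Men join the Extended Dataset by consent after area allocation, at their own provider's invitation, so any comparison by arm of adherence or satisfaction is open to differential selection at entry

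*Protocol article*

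**What the plan says.** All references are to the protocol article.

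- **Order of events.** Areas are allocated under Randomisation. Protocol amendments adds: "Prior to the start of the study, the randomisation of the intervention and control areas were switched". Men are recruited later, and under Extended Dataset, Consent: "Written consent will be obtained from all users prior to their inclusion in this extended data collection phase".
- **Who invites.** Extended Dataset, Recruitment: "Service users will be asked to participate by their service provider (outreach worker, nurse, specialist SSA or pharmacist) during routine consultation". The section on the intervention arm shows where outreach workers operate: "In areas allocated to the 'clinic + outreach' arm, the NHS stop smoking services will attract clients with additional support from four community based stop smoking" (the outreach workers).
- **What kind of sample.** The section on protecting against bias has the secondary questions answered either from service data or from "an Extended Dataset collected from a self-selected sub-sample of participants in the trial".
- **Who measures.** Table 2 has the Call 2 Quit team administer the satisfaction questionnaire. Adherence is recorded weekly by the stop smoking advisor (Table 2; Estimating adherence).
- **Which bias is discussed.** Extended Dataset, Losses to follow-up, reports the services' experience that "individuals who return to smoking do not return to clinic, while those who have succeeded do so and are typically very pleased" with their care. It treats the resulting loss as a potentially major bias and answers it with telephone contact.

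**The concern.** In a cluster trial, randomisation balances the people living in the areas. It does not balance a sub-sample recruited by consent after allocation, when the people doing the inviting differ between arms. Here one inviting role is the intervention itself. An outreach worker can invite a man, treat him and record his adherence, and his service is what the satisfaction questionnaire asks about.

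The protocol recognises that satisfaction goes with success in quitting, but applies this only to men lost after they have joined. The same link matters at entry. If invitation or consent depends on how a man is doing, and does so differently by arm, the arms can differ in adherence or satisfaction with no true effect. A reader of the pilot could then credit the outreach model with a difference that reflects who was asked and who agreed.

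**Working it through.** The document gives no sample size, expected response or other figure for the Extended Dataset, so there is nothing to reproduce. The check is a reading of the sections against each other, a count from Table 3, and an illustration on assumed values.

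**1. Does entry follow allocation?** Yes. The allocation was fixed, and switched, before the study began; consent to the Extended Dataset is sought during consultations after that.

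**2. Do inviters differ by arm?** Yes, for one of the four listed roles. No share of invitations by role is given.

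**3. Do the other inviters know the arm?** Not necessarily. Arm follows area of residence, and many men are treated elsewhere. Sums over the 16 areas in Table 3 (baseline year):

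| Service used | Men | Share of 563 |
|---|---|---|
| In own area | 197 | 35.0% |
| In another randomised area | 36 | 6.4% |
| Outside the study zone | 301 | 53.5% |
| Unidentified | 29 | 5.2% |

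A nurse or pharmacist outside the zone may not know a man's arm. No masking is described either.

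**4. Are the data to be compared by arm?** The sections do not agree.
- The Abstract promises an assessment of the intervention's impact on adherence and satisfaction.
- Question 7 asks about each arm. Question 8 names no arm, but its Table 2 entry counts adherence in each arm.
- Patient experiences describes the satisfaction analysis for the intervention group alone.

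Adherence is therefore by arm; satisfaction is by arm in some places and not in another.

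**5. Does any stated safeguard act at entry?** No. Telephone contact reaches men who have already consented. Call 2 Quit administration separates the satisfaction rating from the provider, again after entry. The statement that information bias is minimal concerns uptake and abstinence only.

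**6. What could selection do? (assumed values)** Let *p* be the true proportion with good adherence, the same in both arms, and *k* the ratio of entry probabilities, men doing well against the rest, in the intervention arm. Take *k* = 1 in control. Then observed proportion = *pk* / (*pk* + 1 − *p*). For *p* = 0.5 and *k* = 1.5: 0.75 / (0.75 + 0.5) = 0.60, a false difference of 10.0 points.

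| *p* | *k* = 1.25 | *k* = 1.5 | *k* = 2 |
|---|---|---|---|
| 0.30 | +4.9 | +9.1 | +16.2 |
| 0.50 | +5.6 | +10.0 | +16.7 |
| 0.70 | +4.5 | +7.8 | +12.4 |

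If *k* is the same in both arms, the difference is 0. If control providers are the more selective, the sign reverses.

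**7. Would standardising on four-week outcome help? (assumed values)** Take a true quit rate of 50%, satisfaction of 90% in quitters and 60% in others, and entry of 80% of quitters and 40% of others.
- True satisfaction: 0.5 × 0.9 + 0.5 × 0.6 = 75%.
- Quitters among entrants: 0.40 / (0.40 + 0.20) = 66.7%.
- Observed satisfaction: 0.667 × 0.9 + 0.333 × 0.6 = 80%.
- Reweighted to the arm's own 50% quit rate: 75% again.

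The recovery is complete only because selection here works through quitting alone. Varying the quit rate (30% or 50%), entry (70/50 to 90/30) and satisfaction (90/60 or 80/40) gives false differences of 2.3 to 10.5 points before reweighting.

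**The case against.** Several stronger readings are tempting, and the document does not support them.

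- *That the outreach worker is usually the inviter, or that every inviter knows the man's arm.* Outreach workers are one of four listed roles with no share given, and 301 of 563 baseline users attended outside the study zone.
- *That inviters pick men by eventual success.* Recruitment mentions a baseline questionnaire, and adherence is recorded week by week. Both suggest entry early in treatment, before the outcome is known. This weakens the mechanism, but no time of entry is fixed, and a provider can judge early how a man is doing.
- *That the provider frame contradicts itself.* Recruitment draws the collecting providers from those "that have, on past data, delivered stop smoking services for Pakistani and Bangladeshi men residing in the intervention or control areas", which newly trained outreach workers could hardly have done in that role. But the same section names outreach workers among the inviters, so the past-activity test is most naturally read as applying to existing NHS providers.
- *That the illustrated differences predict the bias.* They assume selection in one arm only.

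It is also fair to say that a rule on consecutive invitation may sit in the procedure guide supplied to advisors, and that an article need not print it. That stands, so its absence is not the point. What remains is what the article does state: a self-selected sample, invitation by the treating provider, outcomes reported by arm, and a remedy that begins only after consent.

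**Conclusion.** The point holds as a cheap improvement confined to secondary questions 7 and 8 of a pilot. The comparison by arm of adherence, and of satisfaction if it is so compared, is open to differential selection at entry, and nothing described in the plan reduces it. This rests on the stated order of events and the stated inviters, not on any assumed figure.

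The size and direction of any bias cannot be determined from the document. The calculations show only that fairly modest one-sided selection could produce differences of several points.

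A reader might infer that the trial's main results are compromised. They are not: uptake and abstinence come from the service dataset, which needs no individual consent and does not depend on provider invitation.

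**What to change.** 1. **Compare and standardise.** Within each arm, compare Extended Dataset men with all eligible service users on the routinely recorded fields: age, ethnic group, type of service, medication and four-week outcome. Aggregate counts suffice, so anonymised records need not be linked. Report adherence and satisfaction unadjusted and standardised to that arm's own service totals. Using each arm's own totals keeps any real effect on quitting. Limit standardisation to one or two fields, chiefly four-week outcome: 11 of the 16 areas had 11 or fewer baseline users (66 of 563 men), so finer cells would be sparse. State that unmeasured selection remains, and interpret arm differences accordingly.
2. **Reconcile the satisfaction analysis.** Bring Patient experiences, which names the intervention group only, into line with the Abstract, question 7 and Table 2.
3. **For the definitive trial,** have every participating provider, outreach workers included, invite consecutive eligible men at the first consultation. The pilot's intervention period ended on 31 October 2008 (Current study status), so this cannot now help the pilot.

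The cost is one extra analysis and somewhat wider intervals from weighting.

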#### Inclusion criteria

All consenting, self-assigned (using Census 2001 categories)[5] Pakistani and Bangladeshi male adult (≥18 years) regular smokers (defined as self-declared usage of on average ≥1 cigarette/day) using the NHS stop smoking services will be eligible to participate.

#### Exclusion criteria

Any users of the NHS stop smoking services who are not from the relevant ethnic groups will be excluded.

#### Consent

Written consent will be obtained from all users prior to their inclusion in this extended data collection phase.

#### Losses to follow-up

Those individuals recruited in the Extended Dataset will be asked about their satisfaction with the stop smoking service they received. It is the experience of LSSS that individuals who return to smoking do not return to clinic, while those who have succeeded do so and are typically very pleased with the care they received. Thus, loss to follow-up is a potentially major bias in assessing these outcomes. However, these individuals will have consented to follow up and thus we seek to minimise loss of information from those who do not stop smoking by telephone contact from the Birmingham Call 2 Quit line.

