#### Study questions

Primary study questions:

1. What are the rates at which the population of Pakistani and Bangladeshi male smokers will set a quit date with the stop smoking services in the intervention and control areas?

2. What proportions of those setting a quit date in the intervention and control areas achieve biochemically verified prolonged abstinence from smoking at a) 4 weeks, b) 3 months and c) 6 months after the agreed quit date?

3. What is the likely degree of contamination of the intervention and control areas and the design effects that need to be taken into consideration when conducting sample size calculations for a definitive cluster randomised controlled trial?

4. What are the key components of the intervention as it develops and how do these components relate to the outcome measured by the rates of setting quit dates and abstinence among those setting quit dates?

Secondary study questions:

5. What proportion of Pakistani and Bangladeshi male smokers that book an appointment with the stop smoking service attend the initial appointment and set a quit date in the intervention and control areas?

6. What smoking cessation treatments do Pakistani and Bangladeshi men use in the intervention areas, facilitated by outreach workers, and in the control areas, without such workers?

7. What are the experiences of the services of the relevant groups in each of the trial arms and how satisfied are they?

8. What proportions of those enrolled adhere to the interventions chosen?

9. What impact, if any, are these interventions likely to have on smokeless (oral) tobacco use in these smokers?

10. What are the costs, from a health service perspective, of delivering these interventions?

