#### Patient experiences

We have developed a patient satisfaction questionnaire, which will be used to collect information on the experiences of service users. This will be examined for the intervention group using appropriate multilevel models.

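### Satisfaction may be overstated where telephone contact falls short, because the planned analysis makes no stated use of quit status

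*Protocol article*

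**What the plan says.** Satisfaction is a secondary outcome, collected in the Extended Dataset from a self-selected, consenting sub-sample. Study question 7 asks about both arms: "What are the experiences of the services of the relevant groups in each of the trial arms and how satisfied are they".

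The Extended Dataset section on losses to follow-up gives the services' experience: "individuals who return to smoking do not return to clinic, while those who have succeeded do so and are typically very pleased with the care". It concludes that "loss to follow-up is a potentially major bias in assessing these outcomes". Because these men have agreed to follow-up, the stated remedy is that "we seek to minimise loss of information from those who do not stop smoking by telephone contact from the Birmingham Call 2 Quit line". Table 2 gives the data source for question 7 as: "Patient satisfaction questionnaire administered by LSSS 'Call 2 Quit' team".

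The analysis is one sentence under Patient experiences: "This will be examined for the intervention group using appropriate multilevel models".

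On quit status, the inclusion criteria for the Local Stop Smoking Service (LSSS) Dataset state: "The LSSS routinely records abstinence rates at four weeks post quit date". For men not reached, the LSSS section on losses to follow-up sets the rule that "people who are lost to follow-up are deemed to be smoking again". LSSS data reach the researchers anonymised, whereas Extended Dataset data are identifiable. No link between the two is described.

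**The concern.** The article describes a selection mechanism in which one variable, whether the man quit, drives both the chance of being retained and the level of satisfaction. A remedy that aims to reduce the loss leaves bias in proportion to what remains. The analysis it names deals with a different problem: a multilevel model allows for men being clustered in areas. It does not correct for response that depends on quit status unless that status enters the analysis, and no such step is named.

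At stake is the answer to question 7. If non-quitters remain harder to reach, an average over the men who answer describes mainly the successful ones and is likely to be too favourable. That matters for a pilot meant to judge how acceptable the service is before a definitive trial.

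**Working it through.** The article gives no response rate, satisfaction level or sample size for this outcome, so there is no figure to reproduce. The check shows how large the bias could be; every input is an assumption.

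**Notation.** q = proportion who quit; rQ, rN = questionnaire response among quitters and non-quitters; sQ, sN = proportion satisfied in each group.

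- True satisfaction = q·sQ + (1−q)·sN
- Responders only = [q·rQ·sQ + (1−q)·rN·sN] / [q·rQ + (1−q)·rN]

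**Central case:** q = 40%, sQ = 90%, sN = 60%, rQ = 90%.

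- True: 0.4×0.9 + 0.6×0.6 = 72.0%
- rN = 20%: (0.324 + 0.072) / (0.36 + 0.12) = 82.5%, overstated by 10.5 points
- rN = 50%: (0.324 + 0.180) / (0.36 + 0.30) = 76.4%, overstated by 4.4 points
- rN = 70%: (0.324 + 0.252) / (0.36 + 0.42) = 73.8%, overstated by 1.8 points
- rN = 90%: 72.0%, no bias

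**Range of overstatement (points)** with q from 30% to 50%, sQ = 90% and rQ = 90%:

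| Non-quitter response | sN = 50–70% | sN = 80% |
|---|---|---|
| 20% | 6.4–14.3 | 3.2–3.6 |
| 50% | 2.7–5.8 | 1.4–1.5 |
| 70% | 1.1–2.5 | 0.6 |
| 90% | 0 | 0 |

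**Between arms.** Take equal true satisfaction and equal quit rates in both arms (central case).

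- Non-quitter response 30% v 50%: 80.0% v 76.4%, a false difference of 3.6 points.
- Non-quitter response 30% v 60%: 80.0% v 75.0%, a false difference of 5.0 points.
- Equal non-quitter response in both arms: 0.

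If response by quit status is the same in both arms but quit rates are 30% v 40% (sN = 60%), the true difference is 3.0 points. The responders-only difference is 3.0–3.3 points for non-quitter response of 30%, 50% or 90%. The contrast is then almost unbiased even when each arm's level is not.

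**Effect of standardising.** Apply the satisfaction seen among responding quitters and non-quitters to the enrolled mix: 0.4×0.9 + 0.6×0.6 = 72.0%, the true value. This works only if response is unrelated to satisfaction within each quit group. If the calls equalise response, the weights are constant and the estimate does not change.

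**The case against.** **The mechanism concerns clinic attendance, and the questionnaire does not depend on it.** The stated experience is about returning to clinic, whereas the questionnaire is run by the Call 2 Quit team and non-quitters are to be telephoned. This stands. A reader might infer that satisfaction will certainly be overstated; the article does not support that, and if response is equal there is no bias. Nor can success be assumed: under Protocol amendments, the same line was unable to carry out the three-month follow-up. That is a reason for caution, not evidence that the satisfaction calls failed.

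**Absence of a correction is read from silence.** The model is unspecified, and a condensed article may leave non-response methods to a fuller document. This stands in part, and it is why the point is a suggested improvement. But the article itself raises the bias and itself states the analysis, and the two do not meet.

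**Arm bias is speculative.** A reader might infer that outreach would look less satisfying simply because it hears from more relapsed men. That needs non-quitter response to differ by arm. The article describes one telephone line and no such difference, and its analysis sentence covers only the intervention group. The objection stands.

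**Quit status may not be available.** A reader might infer that it is already held for every man. It is routinely recorded by the service, but lost men are assigned to smoking rather than observed, and no link from the anonymised records is described. This also stands. In its favour, Extended Dataset men are consented and identifiable, and their advisors already complete a modified monitoring form, so obtaining status is plausible.

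**Precision is limited.** Table 3 totals 563 baseline users over the 16 areas. If that many all responded, split evenly and 75% satisfied, the 95% margin for an arm difference would be 1.96 × √(0.75×0.25×2/281.5) = about 7 points before clustering, and the Extended Dataset is only a sub-sample. This keeps the point small.

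**Conclusion.** The concern holds as a cheap improvement to a secondary outcome. The article links both loss and satisfaction to quitting and calls the resulting bias potentially major, but relies on telephone contact alone and names no use of quit status in the analysis. Satisfaction may be overstated to the extent that non-quitters still respond less than quitters: about 1–3 points at 70% non-quitter response, 3–6 at 50% and 6–14 at 20%, and nothing if response is equal. These sizes assume 30–50% quitting, quitters 90% satisfied and 90% responding, and non-quitters 50–70% satisfied. If non-quitters are 80% satisfied, the bias is at most 3.6 points.

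The document does not establish that satisfaction will be overstated or that the arms will differ through response alone. One textual conflict is firm: question 7 concerns each arm, while the analysis sentence covers the intervention group only.

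**What to change.** Under Patient experiences:

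- Report questionnaire response by arm and four-week status.
- Present satisfaction by four-week status, and standardised (weighted) to each arm's enrolled mix of quitters and non-quitters, alongside the unweighted estimate.
- Confirm that four-week status is held for all consented Extended Dataset men, including those who do not answer the questionnaire. The intervention period has ended, so status missing from the forms would have to be sought from the services for these identifiable men.
- Separate men observed to be smoking from men counted as smoking because lost. Otherwise unreached quitters fall into the non-quitter group, and weighting could push satisfaction too low.
- Reconcile the restriction to the intervention group with question 7.

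The cost is a little analysis work and a check of data already collected or retrievable. Intervals will be somewhat wider, and some arm-by-status cells will be small. The correction rests on response being unrelated to satisfaction within quit status, and it does nothing about self-selection into the sub-sample; both limits should be stated with the result.
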